# METHODS

## Study area

The intervention will be carried out in the sanitary district of Houndé. This district counts 231.056 inhabitants with a density of 42 inhbts/km2; it includes 7 departments, 99 official villages and more than around thirty migrants' camps. On the medical level, the district counts 27 primary health centres and one hospital district. A baseline survey has demonstrated the importance of child malnutrition in the area and the current inadequacy of health services to tackle it (see box above).

## Study design

The intervention will be evaluated by a pair-matched, cluster-randomized controlled trial . Health facilities, together with the population living in their catchment area, will be matched by pair on the basis of accessibility criteria (distance to the district hospital), functioning criteria (number and profile of health workers, measles vaccine coverage, attendance rates of the growth monitoring programme, utilization rates of health facilities) and population characteristics (households socioeconomic indicators, child morbidity, rates of child wasting and stunting). Scoring of all health facilities will be based on the baseline data, and such score will be used to pair health facilities. Within each pair, one health facility will be randomly allocated the intervention, the other one serving as a comparator.

## The Intervention

### Improving the communicational dimension

A genuinecommunication between health providers and parents is an essential component for the delivery of good quality healthcare. Such communication process, based on a relationship of trust and understanding between the different actors, should address the underlying factors of the health problem and the concrete means to remedy it given the social and familial context.

To improve this aspect, all health workers in the intervention group will be trained on nutrition counselling and child–centeredness. This training will improve health provider skill in detection of feeding problems and negotiation with the mother on possible solutions that she would adopt among a locally adapted set of feeding recommendations .

The training will include two phases:

i) Academic training based on the “Manual on Counselling the Mother”, that includes specific guidance on breastfeeding and complementary feeding counselling (WHO 1997c), as well as on a specific techniques of communication involving all the aspects of the patient - centeredness concept.

ii) Practical training based on case studies in vivo.

This basic training will be reinforced by regular formative supervision sessions carried out by the district director, on a topic identified by the health workers as essential, or on weaknesses identified during the supervisions.

Health workers will be trained by two members staff of the district direction, who will be themselves trained by consultants of the Health Care Department of the Provincial Hogeschool Limburg (PHL): <http://cms.phl.be/eCache/DEF/2/129.html>.

### Improving the functional dimension

*Effective implementation of IMCI*

The health providers in the intervention group will receive training based on the Integrated Management of Childhood Illness Training Manual elaborated by the WHO and UNICEF , with a particular attention on the nutrition component. A regular supportive supervision will be introduced to accompany health workers in the Child illness assessment and care provide. Care will refer to caregiver practices and behaviours changes, Common child illness management, psychosocial stimulation and emotional support.

**Table1. Integrated care provided by first line health services**

**(Derived from WHO/CHS/CAH/98.1A REV.1 1999)**

### Reorganization of health services.

During their lifetime, children encounter a number of time periods during which they are particularly at risk of adverse health outcomes with long-lasting consequences. The intra-uterine period and the first year of life are such critical periods . However, these critical periods are not often acknowledged by health services. The Growth Monitoring and Promotion program for instance implies measuring the children monthly until age 5, i.e. at the same frequency whatsoever the actual age is. As a result, such program is inefficient and eventually not performed . Therefore we proposed to concentrate promotional and screening activities on a number of episodes during the most critical periods.

As early as the 1st antenatal visit, a systematic follow-up plan will be elaborated with the mother. The number of contacts will be standardized to nine for each child (at delivery, 6-8 weeks, 3 months, 4 months, 6 months, 9 months, 12, 15 months, 18 months). At each contact, specific services will be provided.

- **During pregnancy:**

**Table2. Health Sector and Maternal Actions to Improve Maternal Nutrition in Africa (from** )

**At delivery**:

- examine the newborn: general examination based on the IMCI framework; specific examination for sub-luxation of the hip and clubfeet, testicular descent;

- take anthropometric measurements (weight, height); give adequate recommendations as regards the home-management of low birth weight babies;

- promote and support optimal breastfeeding practice;

-promote family planning as a health and nutrition intervention;

- formulate answers to address expressed concerns of parents;

- Correct vitamin A deficiency and anemia in mother;

- vaccinate the newborn (BCG).

**At 6-8 weeks, 3months*, 4 months*, 5 months*, 9 months, 12 months* (*following the vaccination calendar)**:

-examine the infant following the IMCI framework; specific examination for hip dislocation (6-8 weeks);

-take anthropometric measurements (weight, height); discuss the growth pattern of the infant with the parents; investigate the vulnerable factors that may contribute to the potential failure to thrive in each specific case;

-promote exclusive breastfeeding; discuss concerns and difficulties related to breastfeeding and solve them; discuss feeding plans (see table 3); discuss difficulties of implementing the recommendations met by the caretakers;

- vaccinate the infant according to the national vaccination schedule;

- provide vitamin A supplements (12 months)

- ensure adequate malaria prevention (mosquito-net using), general accident prevention; discuss hygiene issues; sensitize, and encourage caretakers to consult quickly when the infant is sick.

- discuss options for family planning.

**At 15 months, 18 months:**

Two supplementary contacts to enhance the feeding practices:

-examine the infant following the IMCI framework; specific examination for hip dislocation (6-8 weeks);

-take anthropometric measurements (weight, height); discuss the growth pattern of the infant with the parents; investigate the vulnerable factors that may contribute to the potential failure to thrive in each specific case;

- discuss feeding practices; discuss difficulties of implementing the recommendations met by the caretakers;

- ensure adequate malaria prevention (mosquito-net using), general accident prevention; discuss hygiene issues; sensitize, and encourage caretakers to consult quickly when the infant is sick.

- discuss options for family planning.

**Table 3: Recommended feeding and dietary practices (derived from Linkages** )

| Infants 0 to 6 months | 􀂌**Initiate breastfeeding within about one hour of birth.**  􀂌**Establish good breastfeeding skills (good positioning and attachment).**  - Baby should be held close to mother, facing the breast, with the  baby’s ear, shoulder, and hip in a straight line.  - Infant’s mouth should open wide just before attaching so the  nipple, and as much of the areola as possible, are in the mouth. If  properly attached, the lips are rolled outward, with the tongue  over the lower gum.  - Signs of effective feeding include visible jaw movement drawing  milk out, rhythmical suckling with an audible swallow, and no  drawing in of cheeks.  􀂌**Breastfeed exclusively** (no prelacteal feeds, no other foods, no  water or other liquids) for about the first six months.  􀂌**Practice frequent, on-demand feeding, including night feeds** (8–  12 breastfeeds per 24 hours, every 2–3 hours, or more frequently if  needed).  􀂌**In areas where vitamin A deficiency occurs, mothers should take**  **a high-dose vitamin A supplement (200,000 IU) as soon as possible**  **after delivery, but no later than eight weeks postpartum, to**  **ensure adequate vitamin A content in breastmilk.** |
| --- | --- |
| Breastfed Children 6 to 24 months | 􀂌**Continue frequent, on-demand breastfeeding, to 24 months and**  **beyond.**  􀂌**Introduce complementary foods beginning around six months of**  **age.**  - Breastfeed before each feeding of complementary food.  􀂌**Increase food quantity as the child ages while maintaining frequent**  **breastfeeding.**  - Provide 6- to 8-month-old infants *approximately* 280 kcal per day  from complementary foods.  - Provide 9- to 11-month-old infants *approximately* 450 kcal per day  from complementary foods.  - Provide 12- to 24-month-old children *approximately* 750 kcal per  day from complementary foods.  􀂌**Increase complementary feeding frequency as the child ages, using**  **a combination of meals and snacks.**  - Feed complementary foods to 6- to 8-month-old infants 2–3 times  per day.  - Feed complementary foods to 9- to 11-month-old infants 3–4 times  per day.  - Feed complementary foods to 12- to 24-month-old children 4–5  times per day.  􀂌**Gradually increase food thickness and add variety as the child ages,**  **adapting the diet to the child’s requirements and abilities.**  - Feed mashed and semi-solid foods to infants, starting around 6  months of age.  - Feed energy-dense combinations of foods to 6- to 11-month-olds.  - Introduce “finger foods” (snacks that can be eaten by children alone)  at about 8 months of age.  - Make the transition to the family diet at about 12 months of age.  􀂌**Diversify the diet of both the breastfeeding mother and the child by**  **including fruits, vegetables, fortified foods, and/or animal products**  **to improve quality.**  - Feed fruits and vegetables daily, especially those rich in vitamin A  and other vitamins.  - Feed meat, poultry, fish, or other animal products daily or as often as  possible (if feasible and acceptable).  - Use fortified foods, such as iodized salt, vitamin A-enriched sugar,  iron-enriched flour, or other staples, when available.  - Give vitamin-mineral supplements when animal products and/or fortified  foods are not available.  􀂌**Practice active feeding.**  - Feed infants directly and assist older children when they feed themselves.  - Offer favorite foods and encourage children to eat when they lose interest  or have depressed appetites.  - If children refuse many foods, experiment with different food combinations,  tastes, textures, and methods for encouragement.  - Talk to children during feeding.  - Feed slowly and patiently and minimize distractions during meals.  - Do not force children to eat.  􀂌**Practice frequent and active feeding during and after illness.**  - During illness, increase fluid intake by more frequent breastfeeding,  and patiently encourage children to eat favorite foods.  - After illness, breastfeed and give food more often than usual, and encourage  children to eat more food at each sitting.  􀂌**Practice good hygiene and proper food handling.**  - Wash caregivers’ and children’s hands before food preparation and  eating.  - Keep all food preparation surfaces clean; use clean utensils to prepare  and serve foods.  - Cook food thoroughly.  - Avoid contact between raw foodstuffs and cooked foods.  - Serve foods immediately after preparation; avoid storing cooked  food.  - Wash fruits and vegetables.  - Use safe water.  - Use clean cups and bowls; never use feeding bottles.  - Protect foods from insects, rodents, and other animals.  - Store non-perishable foodstuffs in a safe place (separate from pesticides,  disinfecting agents, or other toxic chemicals). |

Besides the pre-established schedule of contacts, a home-based follow-up willbe made by the community health agents to families of children:

- missing two consecutive meetings of the follow-up plan

- who haven’t gained weight during the previous 3 months

Those home-visits will aim at assessing care and feeding practice, at reinforcing counselling and at indentifying rapidly a specific need of the children. Possibly, they will also create the opportunity for applying feeding demonstration. The efficacy of such home-visits has been demonstrated in a number of contexts . These community health agents are already available in the field but need to be coached and supported.

**Quality Monitoring of care provided to children and accreditation:**

As demonstrated in our baseline survey, the IMC package is currently not implemented in the health centres of the district, in spite of a previous training of the health agents. The reasons of such discrepancy will be investigated and difficulties met by health agents will be taken into account during a new training round. Quality aspects of health care will be emphasized during the training, and health agents will be accountable for the care provided. In particular, health agents will be invited to audit their practice, notably the way malnourished children have been managed. These audit sessions will be conducted by a team composed of members of the health centre, members of the community, some member of the district team and a social educator, to integrate the clinics and psycho social aspects. This team of audit will meet every two months to review the files of the malnourished children admitted meanwhile. The expected outcome of such process is a continual appraisal of the healthcare by the providers themselves in order to identify and implement possible improvements. Audit reports will be used to orientate supportive supervision and will be one element to deliver the accreditation. Every year health facilities successful in reorganizing their services and fulfilling quality criteria will be delivered a label of “Child Friendly Health Centre”. Such accreditation scheme has contributed to stimulating services upgrade in other settings.

A committee of accreditation composed of a representative of every health centre’s management committee, two representatives of the district team, two representative of the regional direction of the health will be put in place at the beginning of the project.

The following criteria will be used for the range of the centres and will be refined by the committee of accreditation: The rate of frequentation of the health centre, the rate of completive of the follow up plan, the rate of abandonment... The health workers particularly devoted will receive special prices every year. The financing of these prices will be assumed by the different management committee and supported by the project.

**Enhancing the interface between the caretakers and the healthcare providers**

The existing community health workers will be trained to child nutrition, adequate feeding practices, to the key period of the child's life and the specific needs at every period.

They will play and accompaniment role of families with under five children. Each community health worker will be affected to a number of families, and have to:

- follow these families at home and incite them to use the health centre in the setting of the child's systematic follow-up plan and period of disease,
- look for the children who are not regular to the follow-up plan, and identify possible problems and to encourage them to use the health centre,
- Identify cases of home delivery and encourage those families to bring the newborn in the health centre for the follow-up.
- accompany health workers in the home visits for malnourished children
- Assess the nutritional status by measuring the mid-upper arm circumference (MUAC) and refer the children with a MUAC<12, 5 cm to the health centre for further assessment. The purpose is to detect quickly moderate acute malnutrition case for a community ambulatory care.

### Improving the Structural dimension

To date, no structure is in place to manage cases of severe malnutrition. The intervention at this level will be twofold. First, to ensure that cases of severe malnutrition are appropriately managed at the reference level and treated there until they recover to the level of moderate malnutrition; second that cases of moderate malnutrition are adequately managed at the health centre level. The main aims are: to provide effective care for acute malnutrition, by using as much as possible local resources; to improve access and acceptability of the programme for the population; to reduce length of hospitalisation in the health centre, diminishing cross infection.

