**Upgrading the reference hospital paediatric services**

It has been proposed that the WHO guidelines for severe malnutrition are feasible in rural African hospitals, but at the condition of implementing other interventions that build human capital and strengthen the health system .

In order to adequately manage cases of severe malnutrition at the district hospital as recommended by the WHO, the following actions will be undertaken:

- Case detection in the primary health facilities,

- Reference in the district hospital,

- Inpatient care and management of complications in the district hospital,

- Contre-reference in the primary health care as soon as the complication are treated,

- Regular supportive supervision of the primary health care by the district hospital team

- Clinical audit of all case admitted in the district hospital.

Cases of severe malnutrition and cases of moderate malnutrition with complications will enter in program with two phases (the inpatient program and the outpatient program).. Severe malnutrition is defined as W/H<70% or presence of bilateral oedema. Complications are defined as one of the following conditions: anorexia, acute respiratory infection, severe dehydration, severe anaemia, apathy.

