**The inpatient program in the district hospital paediatric services**

The treatment will be essentially based on the OMS standard protocols . However, the WHO guidelines recommend a W/H>90% as criterion of a successful treatment. To reach such a target takes several weeks, exposing the children to possible cross-infections in the hospital and increasing the burden of the parents. Within the current intervention, children will be referred to the primary health centre level for an ambulatory follow-up as soon as the complications are treated and the WH>70%, i.e. when the child is not anymore severely malnourished although not yet completely cured (see point 3.3).

a) Inpatient-treatment phase 1 using only F75 Formula

- Admitted children should be registered and all information recorded in a [Multichart](javascript:plainWindow1()) including the target weight for discharge (WHO/NCHS table).

-Admitted children should be provided with a systematic medical examination and given routine medicine.

- Only F75 will be use during this phase

- Daily surveillance of weight will measured and plotted on the multichart.

- The degree of oedema will assessed and noted in the Multichart,

- Body temperature will measured twice a day

- Standard clinical signs (stool, vomiting, dehydratation, cough, respiration and liver size) will assessed

- Breastfeeding children should always get the breast milk before the diet and on demand.
- Preparation of F75 to give during this phase will based on the class of weight

-The WHO Feeding Table will be used

b) Inpatient-treatment transition using only RUTF

- Daily surveillance of the child remains exactly the same in Transition phase as it was in Phase 1. The expected rate of weight gain is about 6g/kg/day if all the food is taken by the children and there is not excessive malabsorption.

- Breastfeeding children should always get the breast milk before the diet and on demand.
 - Routine antibiotics should be continued after transferred from Phase 1 for another four days.

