***Progress the child to phase 2***

- If the child has a good appetite. Taking 90% of the prescribed RUTF
- If the child has lost the oedema entirely

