**Phase 2 outpatient treatments in the primary health center**

All children with severe acute malnutrition without medical complications and that have passed the [appetite test](http://motherchildnutrition.org/malnutrition-management/info/appetite-test.html) can go directly to Phase 2.

Children that are admitted directly to Phase 2 as out-patients should be provided with a systematic medical examination and given routine medicine.

Children transferred from [in-patient treatment](http://motherchildnutrition.org/malnutrition-management/management-severe-acute-malnutrition/in-patient-treatment-phase-2.html) should be registered as "transferred from".

Surveillance of the children:

- Every week, weight will measure, entered and plotted on the Child Card.
- Every week, the presence of bilateral [oedema](http://motherchildnutrition.org/early-malnutrition-detection/detection-referral-children-with-acute-malnutrition/screening-for-acute-malnutrition.html" \l "Bilateral pitting oedema) will assess and noted in the Child Card.
- Every week, body temperature is measured and noted in the Child Card.
- Every week, standard clinical signs (stool, vomiting, dehydration, cough, respiration and liver size) will assessed and noted in the Child Card.
- Every week, [Mid-Upper Arm Circumference (MUAC)](http://motherchildnutrition.org/early-malnutrition-detection/detection-referral-children-with-acute-malnutrition/screening-for-acute-malnutrition.html" \l "Mid-upper Arm Circumference (MUAC)) will take.
- Every month measurement of height/length

**RUTF** is provided as take-home therapeutic food for malnourished children only.

- The amount of RUTF provided to the caregiver will base on the class of weight and on the necessary quantity required to last until the next visit to the out-patient site.
- Use the RUTF Feeding Table
- Breastfeeding children will always give Breast-Milk before RUTF.
- Move the child in phase 1 (in-patient)
- If the child develops any medical complications that demand in-patient treatment
- If the child has severely reduced appetite
- If the child increases/develops oedema
- If the child develops “refeeding diarrhoea” sufficient to lead to weight loss,
- If the child does not respond to the treatment
- If there is a weight loss for 2 consecutive weighing sessions
- If there is a weight loss of more than 5% of body weight at any visit,
- If the weight stays for three consecutive weighing sessions.

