**Admission criteria:**

**Children from 6 to 59 months for which the P/T<70% or MUAC <110 mm**

**Check for complications and do the appetites test**

**Children with complication and/or failing appetite test.**

1. Bilateral pitting oedema grade 3*(severe oedema)

OR

2. MUAC<110 mm AND bilateral pitting oedema grades 1 or 2 (marasmic kwashiorkor)

OR

3. MUAC<125 mm OR bilateral pitting oedema grades 1 or 2

AND one of the following:

Anorexia

Lower respiratory tract infection

Severe palmer pallor

High fever

Severe dehydration

Fails appetite

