**Return of appetite and reduction of oedema**

Transition phase

In-patient with RUTF

Discharge to follow up

Schema for the decision making process

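### Section 3.3.4 contradicts itself on where severe malnutrition is treated, which children count as severe, and when a child leaves hospital

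*Protocol*

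**What the plan says.** All places are in the Protocol, section 3.3.4 (Improving the Structural dimension) unless stated.

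**Site of care.** The opening paragraph has severe cases managed at the reference level and "treated there until they recover to the level of moderate malnutrition", and gives the health centre the moderate cases. *Upgrading the reference hospital paediatric services* lists referral to the district hospital among the steps. *Phase 2 outpatient treatments in the primary health center* then says "All children with severe acute malnutrition without medical complications and that have passed the" appetite test may go directly to Phase 2. The outpatient branch of the decision schema points the same way, as do the process targets in section 2 and the decentralisation announced in section 4.

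**Who is a case.** Under *Upgrading the reference hospital*: "Severe malnutrition is defined as W/H<70% or presence of bilateral oedema". MUAC plays no part. *Ensuring ambulatory care for moderately malnourished children* defines moderate by W/H alone, between 70% and 80%. The schema's admission criteria read "Children from 6 to 59 months for which the P/T<70% or MUAC <110 mm", with no mention of oedema. The schema box for children with appetite and no complication uses MUAC or oedema, with no W/H.

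**Leaving hospital.** *Upgrading the reference hospital* refers the child back once complications are treated. *The inpatient program* does so "as soon as the complications are treated and the WH>70" per cent. *Progress the child to phase 2* asks for good appetite (90% of the prescribed RUTF) and adds "If the child has lost the oedema entirely". It has no W/H condition.

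**The concern.** These rules decide whether a severely malnourished child is kept in hospital or goes home with therapeutic food, and whether a child gets therapeutic care or feeding counselling. If two paragraphs give different answers for the same child, staff have no single rule to follow. The audit teams that review malnourished children's files (section 3.3.3, quality monitoring and accreditation) have no single standard to audit against.

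There is also an evaluation cost. Section 2 sets targets to halve the annual incidence of severe malnutrition and to reduce the cost of its care. Both need one criterion for what counts as a severe case.

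**Working it through.** The protocol gives no figure to reproduce. The check applies each written rule to the same hypothetical child. P/T is not defined in the document and is taken to mean weight-for-height. The two bullets under *Progress the child to phase 2* are read as both being required. Children A and B are aged 6 to 59 months.

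**1. Site of care. Child A: W/H 65%, no oedema, no complication, appetite test passed.**

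| Place | Reasoning | Result |
|---|---|---|
| Opening of 3.3.4 | 65% < 70%, so severe | Reference level until only moderately malnourished |
| Phase 2 outpatient text | Severe, no complication, appetite passed | May go straight to outpatient care at the health centre |

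**2. Case criteria. Child B: W/H 75%, MUAC 108 mm, no oedema, well, good appetite.**

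| Place | Reasoning | Result |
|---|---|---|
| Upgrading the reference hospital | 75% is not below 70%; no oedema | Not severe |
| Ambulatory care for moderate cases | 70% < 75% < 80% | Moderate: counselling, RUTF can be bought |
| Schema, admission criteria | 108 mm < 110 mm | Meets the admission line |
| Schema, appetite and no complication | MUAC below 110 mm, appetite, well | Outpatient therapeutic care with RUTF |

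The lists of complications, which steer a child to one branch or the other, also differ. Apathy appears only under *Upgrading the reference hospital*. High fever and a failed appetite test appear only in the schema. The first list names acute respiratory infection, the second only lower respiratory tract infection.

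**3. Leaving hospital. Child C: inpatient, W/H 68%, complications resolved, taking 90% of the RUTF, no oedema.**

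| Place | Condition | Result |
|---|---|---|
| Upgrading the reference hospital | Complications treated | Leaves |
| The inpatient program | Complications treated and W/H > 70%; 68% fails | Stays |
| Progress the child to phase 2 | Appetite and no oedema | Leaves |

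Set side by side, A and C show the difficulty. At W/H 65%, child A may start as an outpatient under the Phase 2 text. At the higher W/H of 68%, with complications resolved, child C must stay in hospital under the inpatient text.

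Points 1 and 3 rest on running text. Point 2 rests partly on the schema, whose layout is lost in the text at hand, so links between its boxes are inferred.

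**The case against.** The strongest reply is that the opening of 3.3.4 is an out-of-date overview sentence. The Phase 2 text, the schema's outpatient branch, the section 2 target of managing severe cases in each facility, and the decentralisation in section 4 all favour outpatient care for uncomplicated cases. That may show what the authors intended. It does not remove the contradiction: the overview makes no exception, and the W/H condition in the inpatient text matches it.

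Second, only one sentence calls itself a definition of severe malnutrition, and the schema line is headed as admission criteria. This is fair, and it lowers the weight of point 2. The two still select different children for therapeutic care.

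Third, the rules for leaving hospital could be cumulative. Nothing says so, and two of them are worded to act as soon as their own conditions are met.

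Some stronger readings are tempting but not supported:

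- A reader might set the schema's "Return of appetite and reduction of oedema" against the complete loss of oedema required elsewhere. The schema line most naturally governs the step into the inpatient transition phase, and the other the step out of it, so this is not a conflict.
- A reader might infer that the schema's first line shuts out moderate cases with complications, whom the text and a later schema item admit. That depends on how the boxes connect, which cannot be seen.
- A reader might infer that staff will be trained on incompatible rules. The protocol bases IMCI training on the WHO/UNICEF manual and inpatient treatment largely on WHO standard protocols, so this is a risk and not a stated fact.

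**Conclusion.** The concern holds for site of care and for leaving hospital, with high confidence, because running text contradicts running text. It holds with less certainty for the case criteria, where part of the evidence comes from the flattened schema and P/T is assumed to mean weight-for-height.

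As written, the severe-malnutrition component is not uniquely specified. That bears on patient safety and on what the intervention centres deliver. The severe-malnutrition targets in section 2 lack one consistent case criterion. The documents do not allow an estimate of how many children would be affected; the profiles show only that the rules diverge.

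A reader might go further and call the trial's results uninterpretable. The documents do not support that. Section 3.5 defines wasting separately, by a weight-for-height Z score of −2 or below, so that outcome and its sample size are untouched. Severe-malnutrition incidence and cost are targets in section 2 but are not among the primary or secondary outcomes listed in section 3.6.

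**What to change.** Before training starts, the clinical team should reconcile these parts of section 3.3.4: the opening paragraph, *Upgrading the reference hospital*, *The inpatient program*, *Progress the child to phase 2*, *Phase 2 outpatient treatments*, *Ensuring ambulatory care for moderately malnourished children*, and the decision schema. Text and schema should then share:

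- one case definition, with P/T spelled out;
- one list of complications;
- one route for uncomplicated severe cases;
- one set of criteria for each phase change, stating whether conditions are joined by *and* or *or*.

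The agreed definition should also be applied to the severe-malnutrition targets in section 2. Which clinical rule to adopt is for the clinical team, and none is proposed here.

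The cost is a protocol amendment and matching training material. Sample size and data collection do not change.
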